### Fitness

Aerobic fitness will be assessed in schools using the 20-m shuttle run test [42]. This progressive exercise test involves continuous running between two lines 20 m apart. Audio signals pace the children, beginning at a speed of 8.5 km/h and increasing by 0.5 km/h every minute thereafter. The test ends when the child can no longer keep up with the pace of the beep for two consecutive laps. The shuttle run test provides a valid (r = 0.78) [43] and reliable (ICC = 0.78–0.93) [44] measure of aerobic fitness. Muscular fitness (explosive lower body strength) will be measured using a standing broad jump test. During this test, the child jumps as far forward as possible from a standing position [45], with the best of three jump attempts used in analyses. The standing broad jump test has very high test-retest reliability among children aged 5 to 12 years (ICC = 0.88) [46]. This test is also strongly associated with other lower body muscular strength tests (R^2^ = 0.83–86), as well as with upper body muscular strength tests (R^2^ = 0.69–0.85) [47]. Fitness will be measured using a composite score calculated as the average *z*-scores for the 20-m shuttle run and standing broad jump [48].

### Fatness

Percentage body fat will be measured via InBody 270 Bioelectrical Impedance Analyser (BIA) scales (InBody Co., Ltd., USA). The InBody BIA is a valid (r = 0.69–0.79 for children of this age) and reliable (CV_intra_ = 3%) estimate of body fat compared to underwater weighing [49].

Body mass index (BMI) will be derived from measured height and weight using the World Health Organisation Child Growth Standards [50]. Height and weight will be obtained using a Seca 213 stadiometer (Hamburg, Germany) and InBody BIA scales (InBody Co., Ltd., USA), respectively.

Waist circumference will be measured using a steel Lufkin W606 PM anthropometric tape held at the midpoint between the bottom of the rib cage and the top of the iliac crest. Both waist circumference and BMI have excellent intra- and inter-rater reliability (> 0.88 and > 0.90 respectively) [51]. All measures (percentage body fat, height, weight and waist circumference) will be taken twice. A third measure will be taken if there is more than 0.5 cm, 0.5 kg or 1.0% difference between the first and second measurements, with the mean of two or median of three measurements used in the analyses [52].

### Covariates

Covariates will include age, sex, SEP, parenting style, weight status (where appropriate) and pubertal status. Age, sex, SEP and parenting style will be obtained via a one-off parent questionnaire. Pubertal status will be obtained once per year via parent report.
A composite SEP score will be derived from parent-reported occupation, household income and highest parental education level [53].Parenting style will be reported on three parenting dimensions (warmth, control and irritability) using questions derived from the Child Rearing Questionnaire [54] and the National Longitudinal Survey of Children and Youth [55], based on that used in a study by Wake and colleagues [56].Weight status will be obtained by categorising child BMI as either underweight, healthy weight, overweight or obese using the World Health Organisation Child Growth Standards [50].The Pubertal Development Scale will be used to provide a valid and reliable estimate of pubertal status [57]. For this, parents will be asked to report on their child’s stage of pubertal development based on a number of typical physical indicators associated with pubertal maturation, including the development of body hair, occurrence of growth spurt, and changes in complexion [58]. All questions will be answered on a 4-point scale (1 = has not begun, 2 = has barely started, 3 = is definitely underway, 4 = growth or development is definitely complete) [58].

### Power calculation

Required sample size has been calculated based on Hypothesis 1 (Rates of change in fitness and fatness will differ between in-school and summer holiday periods) using the gold standard of simulation for complex hierarchical models and verified empirically. Power calculations were checked against analytical power calculations for repeated measurements [59] and multi period cross-over designs [60]. Sample size calculations were performed using estimates of the variance components (the variance of random intercepts for schools, students and repeated measurements on students) for the outcome of percentage body fat (%BF), with the aim of being able to detect a meaningful difference in change of %BF of 0.6% per year between the in-school and holiday periods. A required sample size of 300 was estimated using Bonferroni corrected alpha of 0.025 for the two outcomes (fitness and BMI) in conjunction with a power of 0.8 and an assumed drop-out of 25% throughout the follow up.

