### Diet

Dietary intake will be assessed using the Automated Self-Administered 24 h Dietary Assessment Tool (ASA24), Australian version (2016), developed by the National Cancer Institute, Bethesda, MD, United States [33]. The ASA24 is an online tool for collecting 24-h dietary recall data using the seven-pass method (i.e. meal-based quick list, meal gap review, detail pass, forgotten foods, final review, last chance, usual intake) with digital photographic measures to aid portion size estimation [34, 35]. For children younger than 10 years, parent- or proxy-reported dietary intake is required [36, 37]. The ASA24 will be interviewer administered. Parent/carer proxy recalls will be undertaken via phone with the child present where possible so children can provide information on food and drinks consumed in the absence of the parent/carer. At each study time point, parents/carers will complete the ASA24 on one occasion (~ 30 min/recall), recalling food and drinks consumed over the previous 24-h. At the group level weekday and weekend days will be recalled. A second recall will be collected in a sub-sample of 10% to enable estimate of usual intake. Compared to dietary intake assessed via the plate wastage method, the ASA24 estimates energy intake within 0.52 kcal (95% CI − 236, 237) when self-administered by adults (i.e. parents/carer) [38]. Food group intake, energy and nutrient intake will be estimated using the Australian Food Supplement and Nutrient Database (AUSNUT) 2011–3 [39]. Usual energy and macronutrient intake will be derived using the web-based statistical modelling technique Multiple Source Method [40, 41].

Primary outcomes will be fitness and percentage body fat. Waist circumference and body mass index will be assessed as secondary outcomes.

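### Optional efficiency gain: if the 0.025 per outcome used for sizing is carried into the Hypothesis 1 tests, Holm would keep the same family-wise error and give more power

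*Protocol article*

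**What the plan says.** The Power calculation section of the protocol article sizes the study on Hypothesis 1: "Rates of change in fitness and fatness will differ between in-school and summer holiday periods". It then states: "A required sample size of 300 was estimated using Bonferroni corrected alpha of 0.025 for the two outcomes". A parenthesis names the two outcomes as fitness and BMI, and the sentence ends "in conjunction with a power of 0.8 and an assumed drop-out of 25% throughout the follow up". The target effect is "a meaningful difference in change of %BF of 0.6% per year between the in-school and holiday periods", so the effect size concerns percentage body fat only.

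The last paragraph of the Diet section declares the outcomes: "Primary outcomes will be fitness and percentage body fat". It continues: "Waist circumference and body mass index will be assessed as secondary outcomes". The Fitness section defines fitness as one composite, the average of two z-scores.

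The Analysis section describes the mixed model and the contrasts for Hypothesis 1. It gives no significance level and no rule for handling two outcomes.

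**The concern.** Because no other level appears anywhere in the article, 0.025 for each outcome is the one an analyst would naturally carry from the power section into the tests. Used that way, each outcome is judged alone against 0.025. An outcome with p = 0.03 would then count as negative even if the other outcome were overwhelmingly positive.

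Holm removes that loss. It compares the smaller p-value with 0.025 and, if that passes, the larger with 0.05. It rejects whatever Bonferroni rejects and sometimes more.

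The gain arises where both effects are real. That is the study's working premise, since the Background expects fatness to rise and fitness to fall faster over the summer. What is at stake is the chance of showing both effects, at no cost in children or measurements.

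**Working it through.** **Inputs.** From the Power calculation section: alpha 0.025 per outcome, power 0.80, drop-out 25%, N = 300, target 0.6 %BF per year. Assumed because the article does not state them:
- two-sided tests (the hypothesis is non-directional);
- 80% power at 0.025 for fitness as well as for percentage body fat;
- the correlation between the two test statistics, varied from -0.5 to 0.8, with each statistic signed so that its expected effect is positive.

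**The plan's own figure.** 0.05 / 2 = 0.025, which reproduces exactly. The two levels sum to 0.05. With independent tests the family-wise error is 1 - 0.975² = 0.0494. N = 300 can be neither confirmed nor refuted, because the variance components are named without values.

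**Why Holm controls the error.** If both nulls are true, a false rejection needs the smaller p-value to be at or below 0.025, which has probability at most 0.025 + 0.025 = 0.05. If one null is true, its p-value must be at or below 0.05 to be rejected, which again has probability at most 0.05. Neither step uses the correlation.

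**Power with independent tests.**
- Noncentrality: 2.2414 + 0.8416 = 3.083.
- Power at 0.05 with the same noncentrality: Φ(3.083 - 1.960) = Φ(1.123) = 0.869.
- Chance of passing 0.05 but not 0.025: 0.869 - 0.800 = 0.069.
- Holm, per outcome: 0.80 + 0.069 × 0.80 = 0.855, against 0.80.
- Holm, both outcomes (both pass 0.05 and at least one passes 0.025): 0.869² - 0.069² ≈ 0.751, against 0.80² = 0.64.

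**Power by correlation** (simulation, 2,000,000 draws per setting, both effects real):

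| Correlation | Per outcome, Bonferroni → Holm | Both, Bonferroni → Holm | At least one, either rule |
|---|---|---|---|
| -0.5 | 0.800 → 0.865 | 0.609 → 0.739 | 0.992 |
| 0 | 0.800 → 0.855 | 0.640 → 0.751 | 0.960 |
| 0.5 | 0.800 → 0.846 | 0.687 → 0.778 | 0.913 |
| 0.8 | 0.800 → 0.837 | 0.729 → 0.804 | 0.871 |

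**Only one effect real.** At correlation 0, power for the real effect goes from 0.800 to 0.802. The false rejection rate for the other outcome is 0.025 under Bonferroni and 0.045 under Holm, still within 0.05.

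**Neither effect real.** The family-wise error is the same under both rules: 0.0495 at correlation 0 and 0.0467 at correlation 0.5.

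**The case against.** A reader might infer that the protocol commits to testing each primary outcome at 0.025. It does not say so. The sentence describes how the sample size was estimated, and the article contains no decision rule. An analysis plan that is not shown could specify Holm without contradicting the article, because sizing at 0.025 is also the usual cautious choice when Holm is used. This objection stands, and it makes the point conditional.

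A reader might also infer that the multiplicity correction is wrong or that 300 is the wrong number. Neither follows. Bonferroni at 0.025 controls the family-wise error under any dependence, and nothing in the comparison with Holm calls for a different sample size. Choosing between two valid procedures is a question of efficiency.

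The size of the gain is open to challenge too. The article gives no effect size or variance for fitness, so 80% power for that outcome is an assumption. The gain shrinks as positive correlation grows: the increase for both outcomes is 11 points at correlation 0 but 7.5 points at 0.8. This stands, which is why a range is given.

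Finally, the two outcomes in the power section are not the two declared primary outcomes, since BMI is listed as secondary. Adopting Holm would not cure that mismatch. It must be settled so that the rule applies to a defined pair.

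**Conclusion.** This is an optional improvement. The article states one valid multiplicity adjustment and no other level. If that adjustment becomes the testing rule by default, Holm does the same job with equal or greater power.

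On the assumptions listed, and with both effects real, the gain is about 4 to 6.5 percentage points per outcome. For showing both effects it is about 7.5 points at correlation 0.8, 11 at correlation 0 and 13 at correlation -0.5. Power for at least one rejection does not change, and if only one effect is real the gain is practically nil.

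The count of two tests holds only if the fitness composite, rather than its two component tests, is what is tested.

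**What to change.** Keep 0.025 as the sample-size alpha and keep N = 300. Before outcome data are analysed, add one sentence to the Analysis section or the analysis plan, for example:

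> The two primary outcomes for Hypothesis 1, the fitness composite and percentage body fat, will be tested by Holm's procedure at a two-sided family-wise level of 0.05: the smaller p-value is compared with 0.025 and, if significant, the other with 0.05.

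Also reconcile the pair named in the Power calculation section with the primary outcomes declared at the end of the Diet section.

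The cost is the sentence and one loss in presentation. When the second outcome is rejected with a p-value between 0.025 and 0.05, its simple 97.5% interval still includes zero. Because the main results are estimated contrasts, the report should say that intervals and Holm decisions can differ for that outcome.

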### Analysis

Hypothesis 1 (Rates of change in fitness and fatness will differ between in-school [S] and summer holiday [H] periods) will be analysed using linear mixed effects modelling, with the rate of change in fitness and fatness across the in-school period (∆S) and holiday period (∆H) fitted as marginal fixed-slope effects, with age, sex and weight status (where appropriate), as covariates and random intercept and slope coefficients for student, class and school to account for repeated measurements and clustering at different levels of the hierarchy.

Differences between rates of change during in-school and holiday periods (∆_S–H_) will be calculated using model parameter estimate contrasts. We will test Hypothesis 2 (∆_S–H_ differs by SEP, sex and weight status) using similar model parameter estimate contrasts from the linear mixed effects models, with S–H as the dependent variable, and SEP, sex and weight status as the grouping factors (individually and conjointly), and age, sex and weight status where appropriate as covariates.

Rates of change in outcomes during in-school periods (∆_S_) will be operationalised as the change per unit time between the February and December measurements. Rates of change in the summer holiday period (∆_H_) will be operationalised as the change per unit time between the point where the fitted line connecting the February and December measurements intersects with the start of the summer holidays, and the point where the fitted line connecting the February and December measurements of the following year intersects with the end of the summer holidays of the previous year (Fig. 2). This procedure estimates the unmeasured change between the December measurement and the end of the school term, and between the start of the school term and the February measurement.

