**Fig. 2 Fig2:**
[figure not shown]
Mock data for changes in aerobic fitness. The blue shaded areas indicate the holiday periods. The black dots are measured values; the white dots are estimated fitness levels when extrapolated to the start, or back-extrapolated to the end of the holiday periods

Time use will be quantified as 24-h activity compositions [61]. These activity compositions will consist of mutually exclusive and exhaustive parts of the day which together sum up to 24 h. Accelerometry compositions will capture daily times spent in energy expenditure bands (sleep, sitting, light, moderate and vigorous PA), and MARCA compositions will capture times spent in activity “types” (e.g. chores, physical activity, school). The average daily accelerometry and MARCA time-use compositions will be used for analyses. Compositions will be expressed as isometric log ratios [62] to enable their inclusion in the linear mixed effects models. Differences in rates of change in outcome variables (S–H) will be regressed against differences between the in-school composition (C_S_) and the holiday composition (C_H_) (C_S–H_) to test Hypothesis 3 (∆_S–H_ is correlated with C_S–H_). Compositional isotemporal substitution analysis [63] will be used to quantify the change in fitness and fatness when replacing a given quantum of one component of the activity composition (e.g. 30 min of sitting) with the same quantum of another (e.g. 30 min of moderate- to vigorous- intensity physical activity), while holding the remaining components constant. A similar analysis will be performed for diet, with macronutrient mix or food group intake as the composition, and total energy intake as a covariate. Analyses will adjust for age, sex, SEP, parenting style, weight status, and pubertal status, where appropriate.

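### Hypothesis 2 is described in two incompatible ways and Hypothesis 3 uses a derived S–H that needs four consecutive visits; interactions in the Hypothesis 1 mixed model would use all the data

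*Protocol article*

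**What the plan says.** All of this is in the protocol article, in the Analysis section and its continuation after Fig. 2.

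- **Hypothesis 1** is one linear mixed model with an in-school slope and a holiday slope as fixed effects. S–H is a contrast of the two.
- **Hypothesis 2** is to use similar contrasts from the mixed models, but "with S–H as the dependent variable, and SEP, sex and weight status as the grouping factors". The Abstract mentions only the contrasts.
- **Hypothesis 3**: "Differences in rates of change in outcome variables (S–H) will be regressed against differences" between the in-school and holiday compositions. The compositions are log-ratio transformed so that they can enter the mixed models.
- **Definition of the rates**: the in-school rate is the February-to-December change per unit time. The holiday rate runs from that line, extended to the start of the holiday, to "the point where the fitted line connecting the February and December measurements of the following year intersects" the end of the same holiday. The Fig. 2 legend shows measured points and points extrapolated from them.
- **Missing data**: the Power calculation section assumes "an assumed drop-out of 25% throughout the follow up". The article does not say how a child with missing visits is handled under Hypotheses 2 and 3.

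**The concern.** In a mixed model for measured fitness or fatness, the response is the measurement and S–H is a combination of coefficients. If S–H is the response, a value must first be computed for each child. The Hypothesis 2 sentence describes both, and the two can give different analysed sets and different standard errors.

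The two-line definition determines who can have a computed value. One holiday rate needs both visits in each of two adjacent years. A child seen in February, December and the following February spans a summer but has no second line, so no S–H. The Hypothesis 1 model would use those three visits.

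Two things are at stake. One is precision for the effect-modifier and diet/time-use hypotheses, which the sample size was not based on. The other is the missing-data assumption: a likelihood-based mixed model on all observed visits is valid if data are missing at random, while restriction to children with four consecutive visits generally needs a stronger assumption.

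**Working it through.** **1. The plan's own figure.** The sample size of 300 was obtained by simulation for Hypothesis 1. The variance components are named ("the variance of random intercepts for schools, students and repeated measurements on students") but not given, so it cannot be reproduced. Only the drop-out step can be checked: 300 × 0.75 = 225, and 225 / 0.75 = 300. Working back from a two-sided alpha of 0.025 (sidedness assumed) and power 0.8, z = 2.241 + 0.842 = 3.083. The target difference of 0.6 %BF per year therefore implies a standard error of 0.6 / 3.083 = 0.195. With 225 completers and no clustering, the implied child-level SD of S–H is 0.195 × √225 ≈ 2.92 %BF per year. None of this concerns Hypotheses 2 or 3.

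**2. Who has an S–H under the stated drop-out.** Two visits a year for three years give six visits and two summers. Assume the 25% is spread evenly over the five intervals, so 5% (15 children) leave in each.

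- Leave before visit 2, 3 or 4: 3 × 15 = 45 children, no S–H (15%).
- Leave before visit 5 or 6: 2 × 15 = 30 children, first summer only.
- Complete: 225 children, both summers.
- Computable: 225 + 30 = 255 of 300.

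The count depends on when children leave: 225 if all leave before visit 4, 300 if all leave after it.

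**3. Adding intermittently missed visits (assumed rate p at each follow-up visit).**

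P(computable) = 0.85(1−p)³ + 0.75(1−p)⁴ − 0.75(1−p)⁵

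- p = 5%: 0.729 + 0.611 − 0.580 = 0.759, or 228 children (24% lost).
- p = 10%: 0.620 + 0.492 − 0.443 = 0.669, or 201 children (33% lost).

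**4. Standard error of mean S–H.** Assumptions not in the article:

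- holiday of 6–7 weeks, visits about 1.5–4 weeks from the term boundary;
- random child intercept, with or without random child slopes;
- no class or school clustering, data missing at random;
- each child's average S–H counted equally in the two-stage analysis.

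The comparator is generalised least squares on all observed visits: Var = k′(Σ Xᵢ′Vᵢ⁻¹Xᵢ)⁻¹k, where k picks out the in-school minus holiday slope. Example for a common in-school slope, random intercept only and residual SD 1: 0.651 two-stage against 0.588 for the mixed model, a ratio of 1.107. Without random slopes this ratio does not depend on the residual SD, so the absolute values say nothing about the adequacy of 300.

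| Scenario | Two-stage SE vs one model, year-specific in-school slopes | vs one model, common in-school slope |
|---|---|---|
| Complete data | no loss | about 5% larger |
| 25% drop-out, even | about 5–6% larger | about 10–11% larger (about 8% at the lowest, with random slopes) |
| plus 5% of visits missed | about 12–13% larger | about 17–18% larger |
| plus 10% of visits missed | about 19–21% larger | about 24–26% larger |

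The absence of loss with complete data is expected: three in-school slopes, two holiday slopes and an intercept are six mean parameters for six visits, so that model reproduces the two-line estimate. In the common-slope comparison under even drop-out, excluding the 45 children accounts for only about 4% of the information. The rest comes from not pooling the yearly lines and from equal weighting. Weighting children by their number of summers would lower the example ratio from 1.107 to 0.640 / 0.588 = 1.088.

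**The case against.** The best defence is that one mixed model is already intended. The Abstract and half of the Hypothesis 2 sentence say contrasts from the model, and the compositions are transformed for use in mixed models. On that view the dependent-variable phrase is loose wording for the estimand. This may be so for Hypothesis 2, and it is why the finding there is a contradiction rather than a wrong method. It is less convincing for Hypothesis 3, where S–H most naturally reads as a derived outcome.

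A reader might infer several stronger points that the article does not support:

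- **That incomplete children will be dropped.** This follows from the definition if S–H is computed child by child. It is not stated, and missing-data handling may be in a document not shown.
- **That one-summer and two-summer children count equally.** This is an assumption of the calculation. A mixed model with one S–H per summer would give two-summer children more weight.
- **That the two-line method has no benefit.** Year-specific lines avoid assuming one in-school slope over three years of growth. About half of the 10–11% comes from making that assumption in the comparator.
- **That a December-to-February change is a measured holiday change.** It includes term time at both ends, which is what the extrapolation is meant to remove.
- **That 300 children are too few.** The sample size rests on Hypothesis 1, and no power figure is stated for Hypotheses 2 or 3.

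The size is also for mean S–H, not for a group interaction or a composition effect. For Hypothesis 3, a child who leaves before the first holiday measurement has no composition difference and is lost to either analysis.

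**Conclusion.** The concern holds in limited form. The Hypothesis 2 sentence must be reconciled with itself, and the Hypothesis 3 analysis as worded uses a derived outcome that needs visits 1–4 or 3–6. With the article's drop-out spread evenly, about 15% of children have no S–H. The standard error of mean S–H is then about 5–6% larger than a year-specific-slope mixed model would give, or about 10–11% larger than a common-slope model. The loss reaches about 12–26% only under an assumed 5–10% of missed visits. All figures rest on assumed visit timing and data missing at random, and are only indicative for Hypotheses 2 and 3. The loss is modest, but the change needs no extra data and puts the hypotheses in one model.

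**What to change.** - Delete "with S–H as the dependent variable, and SEP, sex and weight status as the grouping factors" as a description of the response, keeping SEP, sex and weight status as the grouping factors.
- Fit one piecewise-linear mixed model to all measured values, using actual visit dates and knots at the start and end of each summer holiday.
- Test Hypothesis 2 as group × (in-school slope − holiday slope).
- Test Hypothesis 3 as isometric log-ratio difference × (in-school slope − holiday slope), in children with an observed composition difference.
- State whether in-school slopes are year-specific or common across years.
- Keep the two-line construction of Fig. 2 as an illustration.

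The cost is a rewording of the Analysis section and slightly more modelling work, with no extra data. A common in-school slope gives the larger gain but adds an assumption. Year-specific slopes avoid it and give up some of the gain.

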## Background

One in six children in OECD countries is classified as overweight or obese [1]. Overweight or obese children are at increased risk of developing non-communicable diseases [2], thereby establishing childhood overweight and obesity as a serious public health concern. There is also evidence showing that children’s aerobic fitness is worse today than several decades ago [3]. Childhood fatness as well as lower muscular and aerobic fitness track moderately well into adulthood, being associated with poorer adult health and higher mortality [4, 5]. Thus, strategies to address overweight and obesity and increase aerobic and muscular fitness levels during childhood are warranted.

Emerging research, predominantly conducted in North America, shows that increases in fatness and declines in aerobic fitness occur at a much greater rate during the school summer holiday period, compared with the school year [6–10]. These negative health outcomes are more pronounced among children who are already overweight or obese or from low socio-economic backgrounds [6]. Thus, the school summer holiday period is identified as a high-risk period for unfavourable changes in body composition, and declines in aerobic fitness, and may be an overlooked critical window for intervention.

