### Aims and hypotheses

The focus of this research is to determine rates of change in fitness and fatness during in-school and summer holidays across successive school years, and to relate rates of change in these outcomes to changes in diet and time use. Specific hypotheses are:
Rates of change in fitness and fatness will differ between in-school and summer holiday periods.The difference between in-school and summer holiday rates of change in fitness and fatness will differ according to the child’s socio-economic position (SEP), sex and weight status.Differences in rates of change in fitness and fatness between in-school and summer holiday periods will be associated with differences in diet and time use between in-school and holiday periods.

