### Measures

The schedule of assessments across the study period is shown in Fig. 1. Diet and time use (accelerometry and 24-h recall) assessments will be conducted at the beginning (Term 1) and end (Term 4) of each school year and during each summer holiday period (December/January) for study years 1 and 2. Anthropometric and fitness measures will be taken at the beginning and end of each school year. Trained research personnel will administer fitness and fatness assessments in school, during usual school hours.

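### Weight status taken from BMI at any one measurement visit would put a regression-to-the-mean difference into the Hypothesis 2 fatness contrast, with sign and size set by the visit chosen

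*Protocol article*

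**What the plan says.** Under Aims and hypotheses, Hypothesis 2 states that the difference between in-school and holiday rates of change "will differ according to the child’s socio-economic position (SEP), sex and weight status". The Analysis section tests this with "SEP, sex and weight status as the grouping factors". The phrase about appropriateness in that sentence qualifies the covariates, not the grouping factors.

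The Covariates section defines the group: "Weight status will be obtained by categorising child BMI as either underweight, healthy weight, overweight or obese". It names no visit and does not say whether the category is fixed, updated or averaged.

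The outcomes come from the same readings. Under Measures, "Anthropometric and fitness measures will be taken at the beginning and end of each school year". Percentage body fat is a primary outcome, and "Waist circumference and body mass index will be assessed as secondary outcomes". The Fatness section takes weight and percentage body fat from the same scales.

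The Analysis section describes a linear mixed model with separate in-school and holiday slopes. It also says that the in-school rate "will be operationalised as the change per unit time between the February and December measurements", and that the holiday rate runs between points extrapolated from each year's February–December line. The two descriptions weight the visits differently, so both are worked through below.

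**The concern.** A child's BMI at one visit is a stable level plus a transient part. Children labelled overweight at a visit have, on average, a transient part above zero there and none at the other visits. If that visit is also an endpoint of the analysed changes, its error passes into the slopes.

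With first-February grouping, the overweight group starts too high. Its in-school slope is pulled down and its holiday slope is pushed up, so S–H is too low. This reads as overweight children getting leaner in school and fatter in the holidays. The Background reports that pattern from earlier work: "These negative health outcomes are more pronounced among children who are already overweight or obese". An artefact could then be taken as confirmation.

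**Working it through.** **The plan's own figure.** The article gives none for this contrast. Its sample size of 300 is for Hypothesis 1 and rests on variance components that it does not print. Only the dropout step can be checked: 225/0.75 = 300.

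**Assumptions (not in the article).** Six complete visits. In fractions of a year: February visit at 0.12, December visit at 0.92, holiday from 0.955 to 1.075. The February–December gap is then 0.80 and the holiday 0.12. 25% of children are overweight or obese. Visit-to-visit BMI reliability R is 0.90 to 0.98; the Fatness section gives only rater reliability, above 0.90. There is no true difference between groups in change.

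**Step 1: weight of each visit's error on S–H** (mean of three school slopes minus mean of two holiday slopes).

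Extrapolation rule, first February:
- School: −1/0.80 = −1.25, over three years −0.417.
- Holiday: the first holiday starts a = (0.955 − 0.12)/0.80 = 1.04375 along the year-1 line. First February therefore enters that holiday slope with weight 0.04375/0.12 = 0.365, over two holidays +0.182.
- S–H: −0.417 − 0.182 = −0.60.

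The one-stage model regresses the outcome on cumulative school time and cumulative holiday time, with a random intercept. First February has weight −0.417 on school and +0.972 on holiday, so −1.39 on S–H. Random slopes do not change these weights when visits are complete.

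**Step 2: error difference between groups at the classifying visit, in BMI SD units.** d = k(1 − R), with k = φ(0.674)/(0.25 × 0.75) = 0.3178/0.1875 = 1.695. At R = 0.90, 0.95 and 0.98, d = 0.170, 0.085 and 0.034.

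**Step 3: false S–H difference (overweight minus other) = d × weight.**

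| Classifying visit | Weight, extrapolation | Weight, one-stage | BMI z/yr at R = 0.95, extrapolation | BMI z/yr at R = 0.95, one-stage |
|---|---|---|---|---|
| Feb, year 1 | −0.60 | −1.39 | −0.05 | −0.12 |
| Dec, year 1 | +4.77 | +5.56 | +0.40 | +0.47 |
| Feb, year 2 | −5.00 | −3.47 | −0.42 | −0.29 |
| Dec, year 2 | +5.00 | +3.47 | +0.42 | +0.29 |
| Feb, year 3 | −4.82 | −5.56 | −0.41 | −0.47 |
| Dec, year 3 | +0.65 | +1.39 | +0.06 | +0.12 |

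First-February grouping at R = 0.90, 0.95 and 0.98:
- Extrapolation: −0.10, −0.05, −0.02.
- One-stage: −0.24, −0.12, −0.05.

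The upper end moves slightly with the assumptions. With 31% overweight (k = 1.65) and a gap of 0.81 (one-stage weight −1.35), R = 0.90 gives 1.65 × 0.10 × −1.35 = −0.22.

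**Step 4: mean of all six visits.** The error difference is then the same at every visit. Each set of weights sums to zero, so the false difference is zero.

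**Step 5: percentage body fat.** Here d = k√(1 − R) × ρσ, where σ is the transient SD of %BF and ρ its error correlation with BMI. The article gives neither. With R = 0.95, σ = 1.0 and ρ = 0.5: d = 1.695 × 0.2236 × 0.5 = 0.19. First-February grouping then gives 0.19 × −0.60 = −0.11 (extrapolation) or 0.19 × −1.39 = −0.26 %BF/year (one-stage).

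**Step 6: cost of leaving out visit 1.** The per-child error variance of S–H is the sum of squared weights times the error variance.
- One-stage: 89.7 rises to 94.3; √(94.3/89.7) = 1.03.
- Extrapolation: without the year-1 line the first holiday is lost, and 96.7 rises to 178.0; √(178.0/96.7) = 1.36.

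**The case against.** The strongest reply is that a condensed article commonly leaves the classifying visit to the full protocol or analysis plan. That stands as far as the omission goes, and the omission is not the point. Every single visit that could be named is an endpoint of the analysed changes, so naming one settles the sign of the bias without removing it.

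The size can also be questioned. Under the extrapolation rule, first-February grouping gives at most about −0.10 BMI z/year. Rater reliability is above 0.90, and each measure is taken at least twice. This stands in part: the first-visit effect is modest. But rater reliability and repeat readings within a visit do not capture day-to-day variation in weight and impedance.

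A reader might infer more than the document supports:
- *That the plan builds in a bias in the direction it hopes for.* No visit is named, December grouping reverses the sign, and Hypothesis 2 is non-directional. The expected direction comes only from the Background.
- *That only the school slope is affected.* The holiday slope carries the artefact too, and in the one-stage model it carries most of it (0.972 of 1.39).
- *That the bias can be set against the 0.6 %BF/year target.* That target belongs to Hypothesis 1, and the %BF shift rests on two unknown quantities.

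**Conclusion.** The point holds for the Hypothesis 2 weight-status contrast with fatness outcomes. Any single-visit classification gives a false S–H difference. At the first February visit it is negative: about −0.02 to −0.10 BMI z/year under the extrapolation rule, or −0.05 to about −0.22 (−0.24 on the first set of assumed dates) in a one-stage model. December visits give a positive difference, and the four visits next to a holiday give larger ones under either method.

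These sizes rest on assumed visit dates, share overweight and visit-to-visit reliability. For %BF the mechanism is the same, but the size cannot be fixed from the article. The mechanism does not carry over to the sex or SEP contrasts, which are not grouped on BMI. Fitness should share little transient error with BMI, so that contrast should be little affected.

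**What to change.** For the Hypothesis 2 weight-status contrast with BMI, waist circumference and percentage body fat, state one of two rules before the analysis:

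- **(a)** Define weight status from the child's mean BMI z-score over all available visits. This removes the error-driven bias when visits are complete (approximately so with dropout) and discards no data. The cost is that the group is no longer a baseline characteristic and partly reflects real change during the study.
- **(b)** Classify at the first visit and leave that visit's fatness outcome out of a one-stage piecewise mixed model. The group stays a baseline characteristic, and the standard error of S–H rises about 3%. Do not combine this with the extrapolation rule, where the first holiday is lost and the standard error rises about 36%.

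Under either rule, report first-visit grouping with all visits as a sensitivity analysis. The change is to the analysis text only and needs no new data.
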